### Exclusion Criteria

O2 dependence, angina, unstable cardiac conditions, unstable diabetes, major medical conditions, claudication, febrile illness, pregnancy or cognitive impairment.

**Sample size calculations **based on the ability to detect significant differences in the key outcome variables with 80% power and p < 0.05 are indicated in table 1. Cardiac risk data was taken from the pilot study and adherence to European guidelines for lifestyle participation in a high risk CVD group was taken from baseline data of the first 50 subjects recruited to the CRAFTS trial. The formulae for detecting change in % was n > = K [P_1_(1 - P_1_) + P_2 _(1-P_2_)]/Δ^2^. The formula for detecting a change in means was n >= 2Kσ^2^/Δ^2^K = 7.8. Our pilot study [27] resulted in a withdrawal rate of 5% overall. Based on primary outcome measures of adherence to all three European lifestyle guidelines and cardiac risk score reduction with an anticipated drop-out rate of 10%, 144 participants will be recruited. 72 randomised to the intervention group and 72 to the control group.

**Table 1 T1:** Sample size calculations

	**% adherence to European Guidelines on CVD prevention in high risk group(CRAFTS baseline data)**		**Target change to detect %**	**Sample size per group**
Moderate or vigorous exercise for 20 mins 3 or more times/week	17		Increase by 20%	73
Dietary intake of 3 vegetables portions & 2 fruit portions or more/day	21		Increase by 20%	80
No smoking % in stroke and TIA patient population	85		Increase by 15%	61
% subjects fulfilling all 3 criterion	9		Increase by 20%	56
	**Mean (sd) of baseline measures from pilot study in stroke patients**	**Mean change in intervention group – pilot study**	**Target change to detect**	
Cardiac Risk Score	9.4 (6.80)	1.52	4.0	72
VO2 exercise test	10.87 (1.71)	1.48	1.0	46
HAD – Anxiety subscale	6.13 (3.71)	0.86	1.5	54

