### Data Collection and Statistical Analysis

Data collected will be recorded on a pro-forma collection sheet and will be entered onto Microsoft Excel and the Statistical Package for the Social Sciences (SPSS v12.0). Analysis will be conducted on an intention to treat basis and withdrawals from the programme will be followed up to ensure complete data. A last measurement carried forward method will be used to predict outcome where drop-outs occur [46]. Baseline data will be reported using descriptive and frequency statistics.

Change scores occurring over the 10 week trial period and between baseline and 1 year will be compared between intervention and control groups using:

▪ Independent t tests and one-way ANOVA where data are interval or ratio level and conform to the assumptions of normality i.e. Cardiac Risk Score, VO2, Maximal work output (Watts), Peak Pressure Rate Product, Lipid profile (Total Cholesterol, HDL, LDL, Triglyceride).

▪ Non-parametric tests (Mann Whitney and Kruskall Wallis tests) will be used for ordinal level data (Hospital Anxiety and Depression Scale, Stroke Specific QoL) or where a normal data distribution is not found.

▪ Categorical variables will be analysed using Chi square tests (% smoking, % taking moderate and vigorous exercise 3 times per week, % meeting 2 fruit/3 veg daily guidelines).

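### Table 1 gives 54 per group for HAD anxiety; the protocol's own formula gives 96, so 72 per group lacks the stated 80% power for a 1.5-point difference

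*Protocol article*

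**What the plan says.** The sample-size paragraph of the protocol article sits under Exclusion Criteria. It says the calculations are "based on the ability to detect significant differences in the key outcome variables with 80% power and p < 0.05 are indicated in table 1". For continuous outcomes it gives the formula and constant as "The formula for detecting a change in means was n >= 2Kσ^2^/Δ^2^K = 7.8".

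The HAD anxiety row of Table 1 reads "HAD – Anxiety subscale 6.13 (3.71) 0.86 1.5 54". By the column headings, 6.13 (3.71) is the "Mean (sd) of baseline measures from pilot study in stroke patients", 0.86 is the mean change in the pilot's intervention group, 1.5 is the change to be detected, and 54 is the number per group.

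The planned size is "72 randomised to the intervention group and 72 to the control group", after allowing for 10% drop-out. The article bases that size on two primary outcomes, adherence to all three lifestyle guidelines and the cardiac risk score. The aims at the end of the Background list the HAD scores as a secondary outcome. Under Data Collection and Statistical Analysis, change scores are compared between groups, and non-parametric tests "will be used for ordinal level data (Hospital Anxiety and Depression Scale, Stroke Specific QoL").

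**The concern.** The row's SD, target and sample size do not fit together under the formula printed beside them, and the gap is too large for rounding. The direction matters. The printed 54 lies well below the 72 to be randomised per group, so the outcome looks comfortably powered. The figure that follows from the printed SD and target lies above 72.

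HAD anxiety is one of two secondary outcomes with a sample size in Table 1; the other is VO2. A reader who trusts the row could take a non-significant HAD result as good evidence against a 1.5-point effect. On the printed inputs, the design would miss such an effect about one time in three or more.

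**Working it through.** **Inputs, all from the sample-size paragraph and Table 1:** K = 7.8; 80% power; p < 0.05; HAD anxiety SD 3.71, target 1.5, printed n = 54 per group; 72 per group randomised; 10% drop-out (72 × 0.9 = 64.8, about 65).

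**1. What K means.** (1.960 + 0.842)² = 7.85, which is two-sided 5% with 80% power. One-sided 5% would be (1.645 + 0.842)² ≈ 6.18. So K = 7.8 is the two-sided constant.

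**2. Do the formulas reproduce the table?** For percentages the article uses n ≥ K[P₁(1 − P₁) + P₂(1 − P₂)]/Δ². The target increases are read as percentage points.

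| Row | Calculation | Result | Printed |
|---|---|---|---|
| Exercise | 7.8 × (0.17×0.83 + 0.37×0.63)/0.20² | 72.97 | 73 |
| Diet | 7.8 × (0.21×0.79 + 0.41×0.59)/0.20² | 79.5 | 80 |
| All three criteria | 7.8 × (0.09×0.91 + 0.29×0.71)/0.20² | 56.1 | 56 |
| VO2 | 2 × 7.8 × 1.71²/1.0² | 45.6 | 46 |
| No smoking | 7.8 × (0.85×0.15 + 0)/0.15² | 44.2 | 61 |
| Cardiac risk score | 2 × 7.8 × 6.80²/4.0² | 45.1 | 72 |
| **HAD anxiety** | 2 × 7.8 × 3.71²/1.5² = 214.72/2.25 | **95.4** | **54** |

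Four rows agree to within rounding, so the formulas are being read as intended. The smoking and cardiac risk rows also fail, but both print more patients than the formula needs. HAD anxiety is the only row that prints too few.

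**3. Could another calculation give 54?** With SD 3.71 and target 1.5:

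- one-sided two-sample test: 76
- one-sample or paired form, Kσ²/Δ²: 47.7, so 48
- pilot change 0.86 used as Δ: 291
- two-sample with a 10% drop-out allowance: 105 to 107
- rank test with relative efficiency 0.955 (assumption): 95.4/0.955 = 99.9, so 100
- one-sample form inflated for drop-out: 47.7/0.9 = 53.0. This is close, but it is not the stated formula, and it would give about 26 for VO2 where 46 is printed.

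Turned round, 54 implies K = 54 × 1.5²/(2 × 3.71²) = 4.41. Alternatively it implies a target of √(2 × 7.8 × 3.71²/54) = 1.99. With Δ = 2.0 the formula gives 214.72/4 = 53.7, so 54.

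**4. Power for 1.5 points** (SD 3.71, two-sided 5%, two-sample t test, noncentral t):

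| n per group | Power |
|---|---|
| 54 (printed) | 55% |
| 65 (after 10% drop-out) | 63% |
| 72 (randomised) | 67% |
| 96 (recomputed) | 80% |

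With the rank-test efficiency of 0.955, power is about 65% at 72 and 61% at 65. The normal approximation gives values within about one percentage point of the table.

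**5. Difference detectable with 80% power:** 1.74 points at 72 per group and 1.84 at 65. The article's own formula gives 1.73 and 1.82.

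**6. Sensitivity to the change-score SD.** The analysis compares change scores, while 3.71 is a baseline SD. If the SD is the same at both visits and the baseline–follow-up correlation is r (assumption; the article gives none), the change SD is 3.71 × √(2(1 − r)).

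| r | Change SD | n per group by the formula | Power at 72 |
|---|---|---|---|
| 0.3 | 4.39 | 134 | 53% |
| 0.5 | 3.71 | 96 | 67% |
| 0.6 | 3.32 | 77 | 77% |
| 0.7 | 2.87 | 58 | 88% |

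A correlation of about 0.72 (change SD 2.79) would be needed to arrive at 54.

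**The case against.** **The target may be the misprint.** The formula returns exactly 54 for a 2.0-point target. In that case the sample size is right, and 72 per group has about 89% power for 2.0 points (86% at 65). This stands as far as it goes: the article does not show which entry is wrong. But one of the two printed numbers must be wrong, and the power shortfall for the printed 1.5 points is real on the printed SD.

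**The baseline SD may not apply.** At a correlation of 0.7, 58 per group would be enough and 72 would be ample. This is a fair limit on the power figures. It does not rescue the row, because the article calculates from 3.71 and states no correlation. A low correlation would make matters worse.

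**Drop-out may not reduce the number analysed.** The plan is intention to treat, with follow-up of withdrawals and the last measurement carried forward, so all 72 per group might enter the test. Then 67% is the relevant figure, provided that carrying values forward does not dilute the difference. Even so, it is below 80%.

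**The consequence is limited.** HAD anxiety is secondary and did not determine the 144. The exercise and diet rows, at 73 and 80, already exceed 72, so the table does not present every outcome as covered. This is correct, and it is why the remedy is a correction and not a larger trial. But for HAD anxiety the table does signal adequate power, and on its own inputs it should not.

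**Conclusion.** The concern holds. With the printed SD of 3.71, target of 1.5 and K = 7.8, the requirement is 96 per group. The printed 54 is 44% lower ((96 − 54)/96). At the planned 72 per group, power for 1.5 points is about 67%, or 63% if 10% are lost; the trial detects about 1.74 to 1.84 points with 80% power.

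These figures assume that the baseline SD also serves as the SD of the change score (a correlation of 0.5), two-sided 5% testing, and a t test as an approximation to the planned rank test. If the intended target was 2.0, the 54 is right and the target is the wrong entry. Only the sponsor can say which. The error does not affect the basis for the total of 144.

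**What to change.** Correct the HAD anxiety row of Table 1 in one of two ways:

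- **If 1.5 was intended,** print 96 per group and state that 72 per group gives about 67% power (63% after 10% drop-out).
- **If 2.0 was intended,** print 2.0 as the target and keep 54.

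In either case add a sentence that the trial of 144 detects a difference of about 1.7 to 1.8 HAD anxiety points with 80% power, and say that this takes the pilot's baseline SD as the SD of the change score. If the pilot can supply the SD of change, use it and name the source.

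The cost is one table row and one sentence. Under the first correction, the stated power for a secondary outcome becomes less favourable. The sample size, the outcomes and the analysis stay as they are, and no extra patients are needed.

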### Consent

Subjects will sign an informed consent statement approved by AMNCH and University College Dublin Ethics Committees prior to participation. Consent will also be sought to access medical records in the hospital of admission and also to contact their General Practitioners (GP). The GP's of all consenting participants will be informed of their agreement to participate and will be asked to inform the study team should they know of any contra-indications to exercise. A further medical screening will be provided prior to sub-maximal exercise testing.

### Outcome Measures

The outcomes of interest can be categorised under the following headings:

1. Change in cardiovascular disease risk

2. Change in health behaviour

3. Change in body objective physical status and physical fitness indices

4. Change in self-reported functioning

The variables and measurement instruments which will be employed are summarised in table 2. Measures will be taken at baseline, at completion of the 10 week intervention programme and at 1 year post intervention. Both the short-term and long-term outcomes are illustrated.

**Table 2 T2:** Variables and measurement instruments

	Instrument	Baseline	Post Intervention	1 year Follow up
**Cardiac Risk**				
Cardiac risk score Waist girth	(Wilson et al 1998) [38] Tape measure	√ √	√ √	√ √
Waist girth	Tape measure	√	√	√
Lipid profile (Cholesterol, trigylceride, HDL, LDL)	Biochemical analysis	√	√	√
Blood Pressure	Sphygomanometer	√	√	√
Mortality				√
Non-fatal CVD/CeVD Event				√
**Physical Fitness & Function**				
Resting HR	Polar heart rate monitor	√	√	
Height, Weight, BMI	Weighing Scales & Meter Rule	√	√	√
Aerobic Fitness – VO2	Astrand Rhyming submaximal exercise test with cycle ergometer	√	√	√
Peak Rate Pressure Product	Polar heart rate monitor and Sphygomanometer	√	√	√
**Self-Reported Function**				
Physical activity and exercise participation % taking moderate and vigorous exercise 3 times per week	International Physical Activity Questionnaire(IPAQ) [40].	√	√	√
Health Related Quality of Life	COOP/WONCA Functional health status charts [43] Stroke Specific Quality of Life Index [42]	√ √	√ √	√ √
**Health Behaviours**				
Smoking – % smoking Diet	Self Reported Status Fruit & vegetable servings/day	√ √	√ √	√ √

### (a) Treatment group

The Intensive Rehabilitation Programme will consist of a 10 week schedule. Baseline measures will be taken during week 1, and an individually tailored exercise training programme prescribed. Training intensity will conform to the recommendations of the American Heart Association, American Stroke Association and American College of Sports Medicine guidelines for aerobic training in patients with cardiac risk [22]. During the subsequent 8 weeks the participants will attend twice weekly for one hour individually tailored fitness training (warm up, cycle ergometry (Motomed or Tunturi cycle ergometer) using either the upper or lower limbs, treadmill training, step work at up to 60% of their maximal heart rate). They will also attend the two hour risk reduction lecture and receive smoking cessation, physical activity and diet counselling appropriate to their needs, in accordance with the World Health Organisation (WHO) guidelines [44]. Reassessment will take place on the 10^th ^week.

The exercise sessions will be supervised by a physiotherapist (OL). Exercise will be stopped if any of the following adverse events occur: chest pain, dizziness, malaise, heart rate in excess of 60% maximal heart rate, oxygen saturation levels lower than 90% and request from participant to stop in accordance with American Heart Association guidelines for exercise testing [45]. Staff with cardiac resuscitation and defibrillation training will be on site during the exercise sessions and the cardiac arrest procedures of the community hospital will apply, immediate first aid and emergency services will be called should an adverse cardiac event occur.

### (b) Control Group

Subjects allocated to the control group will have baseline assessment on week 1 and re-assessment on week 10. They will attend the two hour didactic lecture on risk reduction post stroke and stress management.

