**Methods:**

A single blind randomised controlled trial is proposed to examine a primary care cardiac rehabilitation programme for adults post transient ischemic attack (TIA) and stroke in effecting a positive change in the primary outcome measures of cardiac risk scores derived from Blood Pressure, lipid profile, smoking and diabetic status and lifestyle factors of habitual smoking, exercise and healthy eating participation. Secondary outcomes of interest include health related quality of life as measured by the Hospital Anxiety and Depression Scale, the Stroke Specific Quality of Life scale and WONCA COOP Functional Health Status charts and cardiovascular fitness as measured by a sub-maximal fitness test.

A total of 144 patients, over 18 years of age with confirmed diagnosis of ischaemic stroke or TIA, will be recruited from Dublin community stroke services and two tertiary T.I.A clinics. Exclusion criteria will include oxygen dependence, unstable cardiac conditions, uncontrolled diabetes, major medical conditions, claudication, febrile illness, pregnancy or cognitive impairment. Participants will be block-statified, randomly allocated to one of two groups using a pre-prepared computer generated randomisation schedule. Both groups will receive a two hour education class on risk reduction post stroke. The intervention group will receive a 10 week programme of supervised aerobic exercises (twice weekly) and individually tailored brief intervention lifestyle counselling. Both groups will be tested on week one and week ten of the programme. Follow-up at 1 year will assess longer term benefits. Analysis will test for significant changes in the key variables indicated.

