### Randomisation procedure

Since blinding to the cardiac rehabilitation programme intervention is not possible, a randomised, controlled, single-blind trial is proposed. Patients recruited for this trial will be randomly assigned to a cardiac rehabilitation group and a non-cardiac rehabilitation group. Participants will be stratified into Stroke and TIA groups and block randomisation using blocks of 12 will be performed using a computer generated randomisation schedule (SPSS v12.0) prepared by an independent party in advance. Concealed allocation will be ensured through the use of opaque sealed envelopes.

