### Participant Recruitment

Subjects with ischaemic stroke will be recruited from the outpatient Stroke Rehabilitation Unit, Baggot Street Community Hospital, from the 4 community based stroke support groups. TIA subjects will be recruited from a TIA clinic in a tertiary hospital in the greater Dublin. Information leaflets will be distributed to potential subjects fulfilling the inclusion criteria in the Stroke Rehabilitation Unit database, Baggot Street Community Hospital and TIA clinic in AMNCH Hospital, with the consent of the Consultant Neurologist in this centre. Interested subjects will then contact the principle researcher (OL) should they wish to participate. Talks will be given at each support group branch meeting and information leaflets distributed. Participants will then be screened by phone to ensure they fulfil the inclusion criteria and that none of the exclusion criteria apply. The American College of Sports Medicine PARQ [22] questionnaire will be incorporated in the screening process to exclude subjects unsuitable for exercise testing. The General Practitioners of those attending the support groups will be contacted to give permission for patients to attend the programme and to consent to access medical records where necessary. A one week period between the information dissemination and consent will be given to allow due time for participants to consider the study.

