### Ethical Considerations and Confidentiality

The study conforms to the guidelines of University College Dublin Human Research Ethics Sub-committee (Ref HREC-19-06-[name]). Ethical approval has also been obtained from Saint James's Hospital SHJ/Adelaide, Meath and National Children's Hospitals AMNCH Research Ethics Committee (Ref REC: 2008/07/03)

All participants will be volunteers. Informed consent will be sought from participants following the distribution of an information leaflet and screening for exclusion criteria. Participants will be free to withdraw without prejudice at any time. Since the type of cardiac rehabilitation programme under investigation is not currently available to the Stroke/TIA population, there are no ethical considerations relating to the allocation of participants to a control group.

All information collected relating to participants will be confidential and will be stored securely in a locked cabinet in University College Dublin. Participants will be given a code on entering the study. This will be the only link between the participants name and data.

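### Baseline assessment is scheduled in week 1 for participants already described as allocated, so self-reported baselines can depend on the arm

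*Protocol article*

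**What the plan says.** Three places in the protocol article fix the timing of baseline.

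- Abstract, Methods, after describing random allocation: "Both groups will be tested on week one and week ten of the programme".
- (a) Treatment group, within that arm's 10-week schedule: "Baseline measures will be taken during week 1, and an individually tailored exercise training programme prescribed".
- (b) Control Group: "Subjects allocated to the control group will have baseline assessment on week 1 and re-assessment on week 10".

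On allocation, the Randomisation procedure section says that an independent party prepares the schedule in advance, and adds: "Concealed allocation will be ensured through the use of opaque sealed envelopes". It does not say when an envelope is opened relative to baseline. The same section accepts that the intervention cannot be blinded. Observer blinding provides an assessor unaware of allocation at all three time points, baseline included.

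On screening, Participant Recruitment has a phone check at entry: "Participants will then be screened by phone to ensure they fulfil the inclusion criteria and that none of the exclusion criteria apply". The PARQ is part of that step. The Consent section adds: "A further medical screening will be provided prior to sub-maximal exercise testing".

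Table 2 lists smoking and diet as self-reported and takes exercise from the IPAQ. Data Collection and Statistical Analysis compares change scores from baseline between the arms, by intention to treat, with the last measurement carried forward for drop-outs.

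**The concern.** A baseline taken after participants learn their arm is no longer guaranteed to be independent of the arm. Someone who expects supervised exercise and counselling may describe current habits differently from someone who expects a single lecture. Assessor blinding does not help, because the participant supplies the information.

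This touches a primary outcome. The sample size text names adherence to all three European lifestyle guidelines as a basis for the 144 participants, and each of the three components is self-reported. Quality of life is exposed in the same way. The bias does not shrink with more participants, and it cannot be repaired after the data are collected.

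There is a second, smaller consequence. A participant who is allocated but does not attend in week 1 has no baseline, hence no change score and nothing to carry forward, although the analysis is meant to include everyone randomised.

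**Working it through.** **Order of events.** The article gives no figure to reproduce on this point, so the check sets the sections side by side.

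| Step | Where | What is fixed |
|---|---|---|
| Phone and PARQ screening | Participant Recruitment | At recruitment |
| Exclusion screening, then consent | Ethical Considerations and Confidentiality | Screening comes first |
| Allocation | Randomisation procedure | Concealed; time of opening not stated |
| Baseline, intervention arm | (a) Treatment group | Week 1 of the programme |
| Baseline, control arm | (b) Control Group | Week 1, for subjects called allocated |
| Further medical screening | Consent | Before the sub-maximal test; no week, no order relative to allocation |

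The three statements on baseline agree with one another, and no section places baseline before allocation. The plain reading is therefore allocation, then baseline.

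**What the target means.** Table 1 gives 9% of subjects meeting all three criteria and a target increase of 20%. With the article's formula, n = K[P1(1 − P1) + P2(1 − P2)]/Δ², and K = 7.8, P1 = 0.09, P2 = 0.29, Δ = 0.20:

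7.8 × (0.0819 + 0.2059)/0.04 = 56.1, against 56 in Table 1.

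The target is thus an absolute difference of 20 percentage points.

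**Effect of a shifted baseline.** Write the difference in change as

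D = (post_I − base_I) − (post_C − base_C).

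If knowing the arm raises the intervention arm's reported baseline by b, and follow-up reports carry no matching shift, the observed value is D − b. If it raises the control arm's baseline by b, the observed value is D + b. The shift passes through one for one. The article gives no value for b, so the range below is assumed, with D = 20:

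| Assumed b (points) | b/20 | D − b | D + b |
|---|---|---|---|
| 2 | 10% | 18 | 22 |
| 5 | 25% | 15 | 25 |
| 10 | 50% | 10 | 30 |

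Nothing in the article indicates the direction.

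**Which outcomes are exposed.**

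- Self-reported, so exposed: smoking status, fruit and vegetable servings, IPAQ exercise, quality of life.
- Measured by a blind assessor or by biochemistry, so little affected: blood pressure, lipids, waist girth, BMI.
- Cardiac risk score: exposed only so far as smoking status enters it. The Abstract lists smoking among its inputs; aim (i) does not.
- Mortality and non-fatal events: recorded only at 1 year, with no baseline value.

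**The case against.** The best defence is that the sequence is inferred. The words used for the control arm may simply label what that arm undergoes over the whole trial. In (a) Treatment group the order is baseline, then exercise prescription, then eight weeks of training, so the envelope could be opened within week 1 but after baseline. A condensed article may also leave the moment of opening to the full protocol. This stands to the extent that disclosure before baseline is not explicit. It does not dispose of the point, because the article itself puts baseline inside the arm-specific schedules and nowhere before allocation.

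A second defence concerns the analysis. Chi-square tests are named for the lifestyle percentages. If these compare post-intervention proportions alone, a baseline shift does not enter. That is possible, but the sentence introducing the tests says change scores are compared, so the one-for-one shift holds on the stated wording. It is also fair that follow-up self-reports are unblinded whatever the order at baseline, so the remedy removes only part of the self-report problem.

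A reader might go further and infer that the medical screen falls after allocation, so that exclusions depend on the arm and the intention-to-treat set is broken. The article does not support that. The Consent section gives the screen no week, no order relative to allocation and no rule for removing a randomised participant. Suitability for exercise testing is already checked at recruitment (the PARQ "questionnaire will be incorporated in the screening process to exclude subjects unsuitable for exercise testing"), and the ethics section states: "Informed consent will be sought from participants following the distribution of an information leaflet and screening for exclusion criteria". The screen could well precede randomisation. For the same reason, the document gives no basis for any count of participants lost per arm.

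**Conclusion.** The point holds for self-reported outcomes. On its plain reading, the article takes baseline after allocation from unblinded participants, which exposes the lifestyle-adherence primary outcome and quality of life to baselines that can differ by arm. Under an assumed shift of 2 to 10 points, the distortion is 10% to 50% of the 20-point target, in an unknown direction. This rests on three conditions: participants know their arm by week 1, the shift is not repeated at follow-up, and the lifestyle items are analysed as change. It illustrates sensitivity and is not an estimate of bias.

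It would be wrong to infer that every outcome is biased; the measured ones are little affected. Missing baselines among allocated non-attenders are a consequence of the order, but their number is unknown. The plan should be changed on this point, because a primary outcome is exposed and the remedy is cheap.

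**What to change.** Take baseline assessment out of the two arm-specific schedules and describe it once, as a common visit for all consenting participants. State the sequence: consent, further medical screening, all baseline measures, and only then opening of the sealed envelope. Align the Abstract and the sections on the treatment and control groups with that sequence. If some screening must follow allocation, say how a participant screened out at that stage is handled in the intention-to-treat analysis.

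The cost is that the envelope is opened slightly later. The assessments already exist, so no new procedure or staff should be needed. If the trial already works in this order, the change is one of wording only.
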